#### Control group

For ethical reasons, in patients allocated to the control group (standard of care), MedDiet is being recommended as part of the secondary prevention programme that all patients receive after an ACS. Diet recommendations are included in the hospital discharge report, focused on the advantages of the currently used Spanish MedDiet eating pattern. Briefly, the Spanish MedDiet eating pattern also emphasizes the consumption of olive oil, wheat, wine, fresh fruits, vegetables, nuts, rice, legumes and fish and seafood; limited consumption of meat and dairy products; and very limited consumption of cream, butter or margarine sugary drinks, baked goods, industrial pastries and pre-cooked foods or dishes. Although these recommendations are common to both intervention arms, previous evidence demonstrates that in the absence of intensive interventions compliance is limited [33]. Thus, significantly different dietary outcomes are anticipated between the two groups.

Implementing standard-of-care diet recommendations or the MedDiet advice does not require alteration to usual care pathways, including the use of any medication, and these will continue for both trial arms.

### Participant timeline and assessments

The schedule of enrolment, interventions and assessments in accordance with SPIRIT is outlined in Fig. 2.

**Fig. 2 Fig2:**
[figure not shown]
The MEDIMACS schedule of enrolment, intervention, assessments and endpoints in accordance with the SPIRIT guideline

All patients undergo a complete clinical evaluation at baseline and at 3, 6, 9 and 12 months including a careful assessment of classical cardiovascular risk factors (blood pressure, lipid profile, glycaemic control, medication and alcohol and tobacco consumption). In each visit, the New York Health Association functional class, angina symptoms and major cardiovascular events (cardiac death, need for coronary revascularization and hospital admission for acute coronary syndrome) are recorded. In both groups, the food frequency questionnaire (FFQ) and the Mediterranean Diet Adherence Screener (MEDAS—see below) dietary screener are filled, as well as exercise, nitrate consumption and dental hygiene questionnaires are completed at baseline and at 12 months. In the intervention group, these questionnaires are also completed at the 3-, 6- and 9-month follow-up visits. At the end of the 12-month follow-up period, patients will undergo a repeated intracoronary procedure with measurements of optical coherence tomography (OCT) and endothelial function in the target lesion (see Additional file 2). All patients are sampled for blood, urine, saliva, lingual scrapping and whole faeces at enrolment and at 3, 6, 9 and 12 months. Samples are processed and stored at −80 °C for determination of immune status, protein and metabolite profiles and oral and gastrointestinal microbiota (see Additional file 2).

### Assessment of adherence to diet

A detailed plan to quantify compliance to MedDiet in both arms has been designed (Fig. 1) based on the analysis of the 137-item validated food frequency questionnaire (FFQ) and a 14-item dietary screener (MEDAS) [34]. Moreover, biological markers of compliance in a random sample of 25% of the participants will be used to blindly ascertain compliance. Plasma and urine samples will be used to determine plasma fatty acid composition, urinary tyrosol and hydroxytyrosol, urinary resveratrol and ethanol and plasma folate concentrations as markers of compliance [32].

### Outcomes

The primary endpoint of the MEDIMACS trial is the change (from baseline to month 12) in fibrous cap thickness of an intermediate atherosclerotic plaque in a non-culprit vessel (identified as the target lesion), as measured by OCT. OCT allows for a very accurate measurement of fibrous cap thickness, as demonstrated in histological validation studies [35]. Moreover, OCT allows the quantitation of plaque composition, lesion size, thickness of the fibrotic layer, lipid arch, minimal lumen area, calcification, macrophage density and plaque rupture [36]. All measurements of OCT are performed by an external core lab, blinded to the allocated diet group.

Secondary endpoints of the MEDIMACS trial are:
Changes (baseline to month 12) in the minimum luminal area (mm^2^) and intraluminal diameter measured by OCT in the target lesionPresence of anatomic findings related to plaque instability and vulnerability at 12 months identified by OCT in the target lesion (atheroma plaque rupture, erosion or thrombus)Changes (baseline to month 12) in the micro- and macrovascular endothelial function as a marker of early stages of coronary atherosclerosis, measured by a combined flow-pressure guidewire in the target lesion (change in maximum average speed, coronary flow, coronary flow reserve, fractional flow reserve, basal and hyperaemia microvascular resistances, resistance of basal stenosis and hyperaemia, and coronary impedance during the cardiac cycle)Differences between groups in the micro- and macrovascular endothelial function at 12 monthsDifferences between groups in the neointima thickness of the stent in the treated artery (at 12 months)Changes (baseline to month 12) of the immunological status, including innate T and B cell populations (NK, innate lymphoid cells, monocytes/macrophages) and NKT cellsChanges (baseline to month 12) of gene expression of cytokines and epigenetic profiles associated with methylation, histidine decarboxylase and miRNAChanges (baseline to month 12) in the diversity of the T cell receptors using massive sequencing methodologiesChanges (baseline to month 12) of the microbiota abundance and diversity identified using the 16S rRNA massive sequencing approach and the functional analysis of complete metagenomesChanges (baseline to month 12) of the host and microbiota protein and metabolomics profiles using mass spectrometry (MS) and nuclear magnetic resonance (NMR)-based methodsIncidence at 1 year of major adverse cardiovascular events (MACE) defined as cardiovascular death, myocardial infarction or ischemic strokeClinically driven coronary revascularizationKaplan-Meier analysis of MACE (as defined above) and of clinically driven coronary revascularization

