### Participants

Patients admitted at the Hospital General Universitario Gregorio Marañón, Madrid, for an ACS fulfilling inclusion criteria (Table 1) are prospectively enrolled in the study within the first 72 h after hospital admission.

**Table 1 Tab1:** Inclusion and exclusion criteria for the MEDIMACS clinical trial

Inclusion criteria	
1. Equal or older than 18 years	
2. An established diagnosis of ACS based on clinical, electrocardiographic and laboratory criteria	
3. An intermediate (20–60% lumen stenosis) atherosclerotic lesion identified in a non-culprit coronary artery with diameter > 2.0 mm (target lesion) not undergoing percutaneous coronary intervention at the time of the revascularization procedure	
4. Willingness to modify his/her diet	
5. Able to follow up and answer questionnaires	
Exclusion criteria	
1. Thrombolysis in Myocardial Infarction (TIMI) score < 3 in the culprit vessel (unsuccessful revascularization)	
2. Killip classification III/IV	
3. Active systemic infection, chronic inflammatory disease, periodontal disease or treatment with corticosteroids, antibiotics or immunomodulators within the past 3 months	
4. Renal insufficiency with glomerular filtration less than 30 mL/min	
5. Severe hepatic insufficiency (liver cirrhosis in Child B or C stages)	
6. Any comorbidity with life expectancy of less than 1 year	

Trial overview and allocation are shown in Fig. 1. Before undergoing coronary angiography (performed on clinical grounds), patients are informed by clinical cardiologists about the research project and invited to sign the informed consent document. Coronary intervention procedures are indicated. The MEDIMACS intracoronary research diagnostic study is initiated after completing the revascularization procedure of the culprit coronary lesion, when indicated. Only patients showing an intermediate lesion (20–60% of lumen area) in a non-culprit vessel are finally enrolled in the study (see the “Inclusion criteria” section). This intermediate lesion is labelled as the target lesion for the measurement of the primary endpoint. Within the following 12 h, patients are randomized to receive either a high-intensity intervention to promote the traditional MedDiet or standard-of-care recommendations for 12 months.

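### Secondary endpoint 2 counts plaque rupture, erosion or thrombus at 12 months without reference to the baseline OCT of the same lesion; the comparison stays unbiased, but available precision is given up

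*Protocol article*

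**What the plan says.** **Definition.** Under Outcomes, the second secondary endpoint is the presence of "anatomic findings related to plaque instability and vulnerability at 12 months identified by OCT in the target lesion", with rupture, erosion and thrombus named as the findings. Baseline is not mentioned.

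**Neighbouring endpoints.** The first secondary endpoint, on the same lesion and by the same technique, reads "Changes (baseline to month 12) in the minimum luminal area". The third (endothelial function) and the sixth to tenth (immune, gene expression, T cell receptor, microbiota, protein and metabolite measures) are also changes from baseline. The fourth and fifth are read at 12 months only.

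**Baseline imaging.** Participants places the intracoronary research study after revascularisation of the culprit lesion and before allocation: "Within the following 12 h, patients are randomized to receive either a high-intensity intervention". Participant timeline and assessments says that at the end of follow-up "patients will undergo a repeated intracoronary procedure with measurements of optical coherence tomography (OCT) and endothelial function in the target lesion". Outcomes includes "macrophage density and plaque rupture" among what OCT can show, and adds: "All measurements of OCT are performed by an external core lab, blinded to the allocated diet group".

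**Analysis.** The Statistical analysis plan section assigns linear mixed models to cap thickness and to the quantitative physiology and plaque metrics. It names no method for this binary endpoint. The set for catheter-based endpoints is the randomised patients who have the 12-month catheterisation.

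**The concern.** Every patient enters with an ACS, and Background says that coronary plaque complications often come with inflammation of the whole coronary bed. A finding in a non-culprit plaque at the index procedure is therefore possible. If it is still visible at 12 months, it counts exactly as one that arose during follow-up.

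Two things are at stake. First, part of the variation in the 12-month outcome was settled before randomisation, and the definition makes no use of the image that would account for it. Second, the endpoint as worded cannot show whether a difference between arms comes from fewer new findings or from more healing of old ones, which matters in a trial about mechanism.

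**Working it through.** **1. Is endpoint 2 out of line with its neighbours?** Two other endpoints are read at 12 months only. The fourth (endothelial function) is paired with the third, which is its change version. The fifth (stent neointima) has no baseline value, because a stent placed at the index procedure has no neointima yet. Endpoint 2 is thus the only target-lesion measure that has baseline imaging and no version using it.

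**2. Inputs.** The article states no rate, effect or power for this endpoint, so there is no figure of its own to reproduce. Patients per arm follow from 100 randomised 1:1 and the two attrition figures given: 50 x 0.90 = 45 (Sample size) and 50 x 0.55 = 27.5, taken as 27 (Limitations). The rates are assumptions:
- p, baseline prevalence: 5-20%
- q, probability that a baseline finding is still present at 12 months: 20-70%
- r, probability of a new finding when none was present: 3-5%

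**3. Formulas.**
- 12-month prevalence: P = pq + (1 - p)r
- share of 12-month positives carried over from baseline: pq / P
- share of 12-month variance explained by baseline presence: phi² = (pq - pP)² / [p(1 - p)P(1 - P)]
- standard error of the unadjusted risk difference with n per arm: √[2P(1 - P)/n]; with baseline adjustment, multiply by √(1 - phi²)

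**4. Middle case (p = 0.15, q = 0.50, r = 0.03).**
- P = 0.075 + 0.85 x 0.03 = 0.1005
- carried-over share = 0.075 / 0.1005 = 75%
- phi² = (0.075 - 0.0151)² / (0.15 x 0.85 x 0.1005 x 0.8995) = 0.31
- n = 45: standard error 6.3 points unadjusted, 5.3 adjusted
- n = 27: 8.2 points unadjusted, 6.8 adjusted

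**5. Range over the assumed rates.**

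| p | q | r | Carried over | phi² |
|---|---|---|---|---|
| 0.05 | 0.20 | 0.05 | 17% | 0.02 |
| 0.15 | 0.50 | 0.03 | 75% | 0.31 |
| 0.20 | 0.70 | 0.03 | 85% | 0.52 |

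**6. Simulation of the proposed estimator under no diet effect.** The Mantel-Haenszel risk difference stratified by baseline presence was centred on zero, as was the unadjusted difference. Its variance was 0.47 to 0.97 of the unadjusted variance at 45 and 27 per arm, a reduction of about 3% to 53%. In the middle case at 45 per arm the standard error fell from 6.3 to 5.2 points.

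**7. A second set of assumptions.** With new findings at 10% in both arms, prevalence 5-20% and persistence 10-90%, the mean unadjusted difference lay within 0.4 points of zero in every setting. The theoretical variance ratio was 1.00 at persistence 10%, 0.83-0.93 at 50% and 0.47-0.75 at 90%.

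**8. How an imbalance carries over.** If the analysed arms differ by d in baseline prevalence, the expected 12-month difference with no diet effect is d(q - r). In the middle case at 45 per arm, one standard deviation of chance imbalance is √(2 x 0.15 x 0.85 / 45) = 7.5 points, which passes on 7.5 x 0.47 = 3.5 points. The same formula applies if the imbalance comes from who returns for catheterisation.

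**The case against.** **Presence at 12 months is a legitimate question.** The principal objective is plaque vulnerability after an ACS, and Background describes lesion repair and vessel healing after the event. An unhealed rupture at 12 months is a sign of vulnerability and may reflect diet. This stands. It is why the endpoint should be kept, and why new findings alone should not be treated as the measure of instability.

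**A reader might infer that pre-existing findings bias the diet effect.** They do not. Randomisation makes such findings equally likely in both arms, and the simulated null differences centre on zero. Selective return for catheterisation could unbalance the arms, but that comes from the analysis set, not from the definition.

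**A reader might also infer that the plan excludes baseline from the analysis.** The article does not say so. Adjustment of a binary secondary endpoint may be set out in an analysis plan that is not shown. What stands is that the definition, which the article does fix, makes no reference to baseline.

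**The size is assumed, and the endpoint is weak either way.** Both are true. The middle case gives about 4.5 positives per arm at 45 (0.1005 x 45). The difference detectable with 80% power, roughly 2.8 standard errors, is about 18 points unadjusted and 15 adjusted, both above the 10% event rate. Adjustment does not make this a well-powered endpoint; it makes better use of few events.

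**Conclusion.** The point holds as a minor matter of efficiency and interpretation. Endpoint 2 scores new and persisting findings alike although a pre-randomisation OCT of the same lesion exists. The comparison between arms remains unbiased. What is lost is precision: about 3% to 53% of the variance could be removed, if baseline prevalence is 5-20%, persistence 20-70% and new findings 3-5%. None of these rates is in the article. If findings are rare at baseline, or most have healed by 12 months, the loss is close to nil. Baseline imbalance among returning patients is the second reason to use the earlier image, because the article allows for attrition of either 10% or 45% and balance among those analysed is not assured.

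**What to change.** Keep endpoint 2 as the presence of any of the three findings at 12 months, and add:

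1. The blinded core lab scores rupture, erosion and thrombus on the baseline OCT by the same criteria as at 12 months. Outcomes lists rupture among the OCT readings but not the other two, so these may need a further read.
2. Arms are compared with a Mantel-Haenszel risk difference stratified by baseline presence, or with an exact stratified test if counts are sparse.
3. New, persisting and resolved findings are tabulated by arm, without restricting the interpretation to new findings, so that healing stays visible.

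The cost is a change to the wording of one secondary endpoint, one stratified analysis and some extra scoring of images already acquired. No further procedure is needed. Stratification brings little if findings prove rare or mostly resolve.

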### Adverse outcomes

All research staff will report any health problems related to the study at any time. All serious adverse events, whether associated or not with the intervention, will be documented on paper and electronic case report forms. All adverse events will be noted in the publication of the results. An analysis of clinical outcomes after completion of the 12-month follow-up period of the first 50 recruited patients is planned and approved by the Ethical Committee of the Hospital Gregorio Marañón. Although unlikely, they may recommend stopping the clinical trial if relevant safety differences are detected between groups.

### Sample size

The sample size of the MEDIMACS clinical trial has been calculated on the assumption of an expected difference of 40% on the relative change in the fibrous cap thickness of the atherosclerotic plaque from baseline to 12 months between patients undergoing a high-intensity MedDiet intervention in comparison with the standard of care. This magnitude is a 10% lower than the difference previously reported using a similar design in a clinical trial comparing the effect on the fibrous cap of lipid-lowering therapy with 5 mg/day versus 20 mg/day atorvastatin, with an estimated standard deviation of 58% [37]. Based on a two-sample bilateral alpha error of 0.05 and a power of 0.80, the required number of patients is 35 per group. Assuming an attrition rate of 10%, 100 patients are needed to be randomized following a 1:1 allocation ratio. With this sample size, different scenarios could be contemplated under potential deviations from the expected effect size (Table 2).

**Table 2 Tab2:** Alternative scenarios for statistical power with *n* = 100 sample size, assuming 10% attrition rates

Effect size	Power	Comment
50%	100%	Effect addressed in EASY-FIT Study
**40%**	**99.60%**	**Baseline assumptions**
30%	93.45%	Effect 25% relatively lower than expected

Regarding the suitability of this sample size to evaluate the secondary endpoints, micro- and macrovascular endothelial functions are proven to be highly sensitive to detect meaningful effects using small sample populations (50–100 patients) [38, 39]. Microbiota, immunological and metabolic changes in response to diet interventions have been widely reported using small sample populations (20–50 patients), particularly under pathological conditions [40, 41].

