**Methods:**

The MEDIMACS project is an academically funded, prospective, randomized, controlled and mechanistic clinical trial designed to address the effects of an active randomized intervention with the Mediterranean diet on atherosclerotic plaque vulnerability, coronary endothelial dysfunction and other mechanistic endpoints. One hundred patients with ACS are randomized 1:1 to a monitored high-intensity Mediterranean diet intervention or to a standard-of-care arm. Adherence to diet is assessed in both arms using food frequency questionnaires and biomarkers of compliance. The primary endpoint is the change (from baseline to 12 months) in the thickness of the fibrous cap of a non-significant atherosclerotic plaque in a non-culprit vessel, as assessed by repeated optical coherence tomography intracoronary imaging. Indices of coronary vascular physiology and changes in gastrointestinal microbiota, immunological status and protein and metabolite profiles will be evaluated as secondary endpoints.

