### Limitations

Complying with basic ethical principles, the control group will receive standard-of-care diet recommendations which include several aspects of the MedDiet. Other alternatives, such as a low-fat diet, are associated with worse outcomes than MedDiet and would not be ethical to implement in a contemporary clinical trial [3]. We recognize that, for the purpose of MEDIMACS, adherence to MedDiet in the control group may blur the effect of the experimental intervention and decrease the power to detect differences between arms. However, it has been demonstrated that a personalized, professionalised and closely monitored high-intensity intervention is highly effective to promote adherence to traditional MedDiet, whereas general recommendations are much less powerful [20]. Therefore, we anticipate that true adherence to MedDiet specifications will be highly different between both groups. Nevertheless, primary and secondary endpoints will be analysed both by intention-to-treat and by a per-protocol basis. For this purpose, ad hoc biomarkers have been implemented and will provide investigators with robust metrics of diet adherence and efficacy.

The primary endpoint of the trial is based on intracoronary imaging, and therefore, an invasive catheterization procedure is required for obtaining this read-out. Because patients may refuse undergoing this second study, a 45% attrition has been pre-specified. A detailed plan to quantify compliance to MedDiet in both arms has been designed, including validated dietary self-reporting questionnaires and biomarkers. Biomarkers of compliance will be measured in random subset of participants from the two arms of the trial as a potential way of accommodating both systematic and random components of measurement error in dietary self-reporting.

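### Table 2 overstates power: its figures fit 90 patients per arm, but 100 randomised with 10% attrition leaves 45 per arm

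*Protocol article*

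**What the plan says.** All inputs are in the Sample size section of the protocol article. The planned effect is "an expected difference of 40% on the relative change in the fibrous cap thickness", taken "with an estimated standard deviation of 58" per cent. The size per group follows: "Based on a two-sample bilateral alpha error of 0.05 and a power of 0.80, the required number of patients is 35 per group". The total is then set: "Assuming an attrition rate of 10%, 100 patients are needed to be randomized following a 1:1 allocation ratio". The Methods part of the abstract confirms that this total covers both arms: "One hundred patients with ACS are randomized 1:1 to a monitored high-intensity Mediterranean diet intervention or to a standard-of-care arm".

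Table 2 is captioned "Alternative scenarios for statistical power with *n* = 100 sample size, assuming 10% attrition rates". It gives power of 100% for a 50% difference, 99.60% for 40% (marked as the baseline assumption) and 93.45% for 30%.

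**The concern.** The table cannot be squared with the paragraph above it. That paragraph says 35 per group gives 80% power at a 40% difference. Ten more patients per arm cannot raise this to 99.6% on the same SD, alpha and test.

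The table is there to show what happens if the effect is smaller than planned, and the protocol gives reason to expect that. Controls are also recommended a Mediterranean diet (Control group section), and the Limitations section accepts that this may dilute the contrast and cost power. A reader who trusts the 30% row would take a non-significant result as fairly strong evidence against a 30% difference. On the correct figure, about one trial in three would miss such a difference.

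**Working it through.** **Inputs.** SD σ = 58, differences δ = 50, 40 and 30 (percentage points of relative change), two-sided alpha 0.05, N = 100 randomised 1:1, 10% attrition. All are from the Sample size section. Evaluable per arm: 50 × 0.90 = 45.

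**Step 1: reproduce the stated sample size.** n per group = 2(1.960 + 0.842)² σ²/δ² = 2 × 7.849 × 58²/40² = 33.005, rounded up to 34. The t-test also gives 34. The protocol states 35, which has 81.2% power by t-test (82.3% by normal approximation). So the effect, SD and sidedness are read as the authors used them.

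**Step 2: power at 45 per arm.** Normal approximation: power = Φ(δ/SE − 1.960), with SE = σ√(2/n) = 58 × √(2/45) = 12.227.

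- δ = 50: Φ(4.089 − 1.960) = Φ(2.129) = 98.3%
- δ = 40: Φ(3.271 − 1.960) = Φ(1.311) = 90.5%
- δ = 30: Φ(2.454 − 1.960) = Φ(0.494) = 68.9%

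**Step 3: find what reproduces Table 2.** With n = 90 per arm, SE = 58 × √(2/90) = 8.646.

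- δ = 50: Φ(5.783 − 1.960) = 99.99%
- δ = 40: Φ(4.626 − 1.960) = 99.62%
- δ = 30: Φ(3.470 − 1.960) = 93.45%

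| Difference | Table 2 | 45 per arm, t-test | 45 per arm, normal | 90 per arm, normal |
|---|---|---|---|---|
| 50% | 100% | 98.1% | 98.3% | 99.99% |
| 40% | 99.60% | 89.9% | 90.5% | 99.62% |
| 30% | 93.45% | 68.0% | 68.9% | 93.45% |

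Solving n = 2[58(1.960 + z)/δ]² for the printed powers gives 89.4 per arm (40% row) and 90.0 per arm (30% row); the t-test gives 90.4 and 91.0.

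**Step 4: try other readings** (normal approximation; 50% / 40% / 30% rows).

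- 45 per arm, one-sided: 99.3 / 94.8 / 79.1
- 50 per arm (no attrition), two-sided: 99.1 / 93.2 / 73.4
- 50 per arm, one-sided: 99.6 / 96.4 / 82.7
- 100 per arm, two-sided: 100 / 99.8 / 95.5

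None matches all three rows. Only 90 per arm does, and 100 less 10% is 90.

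**The case against.** Four points can be made for the protocol.

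- **The sample size does not rest on Table 2.** It comes from 35 per group, which reproduces, and 45 per arm still gives about 90% power at the planned difference. Recruitment is complete (Trial status), so a corrected table cannot change N. This stands, and it limits the consequence to interpretation.
- **A null result will be read from its confidence interval.** The Statistical analysis plan section promises a 95% interval by asymptotic and bootstrap methods, and that interval, not planned power, shows which effects are excluded. This is fair, and no text says the table will be used to interpret a null result. But the table is published as the trial's robustness statement, and it is wrong in that role.
- **The cause is inferred.** Under the normal approximation the same powers arise at 45 per arm if the factor 2 is dropped from the variance, which equals an SD of 58/√2 ≈ 41. This also stands, so the per-arm mix-up is the likely explanation and not a proven one. It does not rescue the figures: it contradicts the stated two-sample test and SD, and the same slip would have halved the sample size in Step 1 to 33.0/2 = 16.5, or 17 per group, not 35.
- **The 50% row is barely off, and the two methods differ by up to 1 point.** Both are true. The material errors are in the 40% and 30% rows, where the gaps are far larger than any choice of formula.

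**Conclusion.** The point holds. On the protocol's own assumptions, power at 45 per arm is 90% rather than 99.60% at a 40% difference (9 to 10 points too high), and 68 to 69% rather than 93.45% at 30% (about 25 points too high). By t-test the type II risk at 30% is 100 − 68.0 = 32.0%, against 100 − 93.45 = 6.55% implied by the table. The 50% row is overstated by less than 2 points.

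This rests on the stated SD of 58%, the stated two-sided two-sample comparison and the 10% attrition in the caption. The 80% target at a 40% difference remains met under those assumptions.

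The Limitations section gives a different attrition figure: "a 45% attrition has been pre-specified". That conflict is a separate matter and is not needed for this conclusion, but it would lower the powers further. At 55 evaluable patients (27.5 per arm) the t-test gives about 88%, 71% and 47%.

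**What to change.** Replace the powers in Table 2 with 98.1%, 89.9% and 68.0% for differences of 50%, 40% and 30%. State under the table that they are for a two-sample t-test with 45 evaluable patients per arm, SD 58% and two-sided alpha 0.05. If the normal approximation is preferred, the figures are 98.3%, 90.5% and 68.9%; use one method throughout.

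It would help to add a column for the 45% attrition given under Limitations (27 to 28 per arm: about 88%, 71% and 47% by t-test), or to reconcile the two attrition rates first.

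The cost is three corrected figures and a note, with less favourable stated power. Sample size, conduct and analysis do not change.
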